## Abstract

**Background:**

Youth orphaned by HIV in sub–Saharan Africa experience immense hardships including social disadvantage, adverse childhood events and limited economic prospects. These adversities disrupt the normative developmental milestones and can gravely compromise their health and emotional wellbeing. The *Bridges to the Future* study (2012–2018) prospectively followed 1,383 adolescents, between 10–16 years, to evaluate the efficacy and cost-effectiveness of a family-based economic empowerment intervention comprising of child development accounts, financial literacy training, family income generating activities and peer mentorship. Study findings show efficacy of this contextually-driven intervention significantly improving mental health, school retention and performance and sexual health. However, critical questions, such as those related to the longitudinal impact of economic empowerment on HIV prevention and engagement in care remain. This paper presents a protocol for the follow-up phase titled, *Bridges Round 2*.

**Methods:**

The *Original Bridges* study participants will be tracked for an additional four years (2022–2026) to examine the longitudinal developmental and behavioral health outcomes and potential mechanisms of the effect of protective health behaviors of the *Bridges* cohort. The study will include a new qualitative component to examine participants’ experiences with the intervention, the use of biomedical data to provide the most precise results of the highly relevant, but currently unknown sexual health outcomes among study participants, as well as a cost-benefit analysis to inform policy and scale-up.

**Discussion:**

Study findings may contribute to the scientific knowledge for low-resource communities on the potential value of providing modest economic resources to vulnerable boys and girls during childhood and early adolescence and how these resources may offer long-term protection against known HIV risks, poor mental health functioning and improve treatment among the HIV treatment care continuum.

## Introduction

Globally, adolescents and young adults between 14–29 years represent 30% of HIV incidence cases among persons of reproductive age, with the vast majority of cases (~75%) occurring in sub–Saharan Africa (SSA) [1]. HIV incidence rises rapidly in SSA, as adolescents and young adults leave school (often prematurely) and migrate for work and marriage [2–4]. In particular, older adolescents are more likely to experience increased experimentation with health-compromising behaviors that increase their vulnerability to HIV and sexually transmitted infections (STIs), including sexual risk behaviors and alcohol/ drug misuse [5–7]. Young people orphaned by AIDS (YPoAIDS), 80% (~10 million) of which live in SSA represent a particularly vulnerable and unique population [8]. Between 2012–2018, our *Bridges to the Future* study team prospectively followed 1,383 adolescents (10–16 years at study enrollment, who lost one or both parents to AIDS), across 48 primary schools in Uganda, to evaluate the efficacy and cost-effectiveness of a family-based economic empowerment intervention (EEI) comprising of child development accounts, financial literacy training, family income generating activities and peer mentorship. Our findings show short-term success with reduction in multidimension poverty incidence (*b*−0.107, SE = 0.034, p<0.001) [9], improving self-related health (B = 0.25, 95% CI = 0.06–0.43) and emotional well-being, including lowered depression (B = -0.28, 95% CI = -0.43–0.125), hopelessness (B = 0.05, 95% CI = –0.11, 0.21), improved self-concept (B = 0.26, 95% CI 0.09–0.44), and adherence self-efficacy (B = 0.26, 95% CI = 0.09–0.43); reduced self-reported sexual risk-taking behaviors (B = 0.05, 95% CI = –0.11, 0.21) [10,11]; and positive educational outcomes among intervention participants, including better academic performance (*b* = −3.78, 95% CI = −4.92, −2.64, *p* ≤ 0.001) and higher odds of transitioning to post primary education (OR = 1.66, 95% CI = 1.28, 2.18, *p* ≤ 0.001) [9–12]. However, critical questions related to the longitudinal impact of economic empowerment on HIV prevention and engagement in care among YPoAIDS remain.

This *Bridges-Round 2* (*hereafter Bridges-R2*) study proposes to examine the longitudinal impacts of the *Bridges* intervention on HIV risk prevention and care continuum outcomes among orphaned youth transitioning to young adulthood, a period characterized by unique vulnerabilities including increased experimentation, lower social control, and treatment non-adherence for those living with HIV [13,14]. Guided by the life course perspective [15], *Bridges-R2* will build on the *Original Bridges to the Future* study, to examine the longitudinal developmental and health outcomes [e.g., sexual risk-taking behaviors, HIV antiretroviral therapy adherence, pre-exposure prophylaxis (PrEP) use (for those who are HIV negative), optimizing health outcomes along the HIV care continuum, and potential mechanisms of effect of protective health behaviors] of the *Bridges* cohort. The study is guided by the following specific aims:

**Aim 1.** To examine the long-term impact of *Bridges* on: a) HIV prevalence (measured via participant’s HIV status) (primary outcome); and b) Explore in secondary analyses the long-term impact of *Bridges* on key developmental and behavioral outcomes (e.g., mental health, alcohol and drug misuse).

**Aim 2**. To elucidate the long-term effects of *Bridges* on potential mechanisms of change, including: a) economic stability, viral suppression (for adolescents living with HIV); PrEP use (for HIV negative adolescents), medical male circumcision (for boys); and b) young adult transitions.

**Aim 3:** To qualitatively investigate participants’ experiences with *Bridges* that may have influenced engagement with the program, sexual risk-taking decisions, financial behaviors; experiences with developmental transitions; and perceptions on program sustainability.

**Aim 4:** To assess the long-term costs and benefits of *Bridges* using formal economic evaluation.

## Background

Adolescents in SSA suffer more from poverty and high HIV prevalence rates than in all other regions in the world. Despite advances in prevention efforts, including treatment as prevention, HIV testing, and PrEP [16,17], HIV incidence for youth remains high [18] and HIV prevention efforts often remain low [16]. Adolescents living with HIV/AIDS face a) more critical developmental, psychosocial and economic adversities, b) less social support and opportunities for education, and c) compounded risk for mental health, addiction, and HIV-risk struggles than the general population [19–21]. Moreover, an understudied hardship of HIV/AIDS in SSA is the high prevalence of young people, including adolescents, who have lost one or both parents to this virus. Worldwide, there are ~20 million YPoAIDS and nearly 12 million are in SSA [22]. Growing up orphaned poses tremendous challenges, including higher rates of HIV risk behavior, higher odds of acquiring HIV infection and low likelihood to test for HIV than non-orphans [23–25].

Uganda, a fragile and low-resource country in SSA, is highly afflicted with poverty and HIV/AIDS. With an estimated 47 million people, 34.5% of the population live on less than $1.90 a day [26]. Uganda is one of the top 10 countries with the largest number of poor people in Africa [26]. The poverty rate is higher in rural areas–such as the proposed study region, estimated at 33.8% compared to 19.8% in urban areas [27]. Among children, an estimated 56% of Uganda’s children below the age of 18 experience multidimensional deprivation and a low standard of living [28]. In addition, approximately 1.4 million Ugandans are currently living with HIV, ~53,000 new HIV infections occurred in 2019, and nearly 21,000 people died in 2017 because of HIV/AIDS [29]. Moreover, Uganda is highly impacted by orphanhood, with ~1.2 million children orphaned due to AIDS [30]. Young people in Uganda, especially those affected by AIDS, often live in poverty and show high rates of depression [31–33], anxiety, learning challenges [34,35], and sexual risk-taking [36,37]. They often experience stigma related to HIV orphanhood [38], low self-esteem and hopelessness about their future, which can negatively influence decisions about substance use and sexual risk-taking, further increasing HIV vulnerability [39]. Moreover, young people in poverty-impacted families have lower levels of secondary education, higher rates of low-wage work, and more young parenting [40,41], which result in negative outcomes such as unstable housing, substance use, mental health problems, and sexual risk-taking leading to HIV/AIDS [40–42], all of which compromise successful social transitions.

### Emerging adulthood as a precarious developmental period

Emerging adulthood typically defined as ages 18–25 [13], is a precarious developmental period requiring effective early-in-life prevention interventions to promote positive behavioral and health outcomes. Emerging adulthood is characterized by identity formation as well as a feeling of existing “in between” adolescence and adult-stages [14]. It is one of the most challenging transition periods [14]. The ordering, timing, and tempo of these transitions can have health consequences, including HIV risk behaviors, and suboptimal adherence to long-term prescribed medications for youth living with HIV (YLHIV) [40]. Moreover, this age group is also at a higher risk of poor mental health functioning [13,43–45]. Successfully accomplishing developmental tasks during emerging adulthood not only influences immediate functioning, but also lays the foundation for optimal functioning later in life [46,47]. Orphaned youth are particularly vulnerable during this transition period. They are subject to permanent separation from biological parents, multiple relocations, stigma and discrimination associated with orphanhood [29,31,42,48,49]. Moreover, lack of family support may make developmental transitions more difficult [50–52]. Yet, little is known about how YPoAIDS and YLHIV navigate transition into young adulthood. The *Bridges* study of YPoAIDS (recruited at ages 10–16 years) from poor communities in Uganda provides a strategic opportunity to examine this transition period, identify key predictors of positive transitions among YPoAIDS, including YLHIV, and isolate the effect of financial instability on their transition milestones and behavioral health.

### Theoretical frameworks guiding the study

#### Developmental and emerging adulthood

Orphaned youth are subject to a host of risks including, permanent separation from biological parents, often multiple relocations, stigma and discrimination [29,31,42,48,49]. These experiences may interfere with the normal development and disrupt the healthy transition through developmental stages, resulting in disengagement from opportunities, school failure, risk-taking behaviors, poor emotional well-being, and poverty [50,51]. Moreover, lack of family support may make developmental transitions more difficult [50,51]. Thus, interventions aimed at supporting youth living with HIV should focus on increasing self-efficacy and enhanced control over one’s life [50,51].

Within the developmental theoretical framework is the emerging adulthood transitional period, with its associated unique characteristics and vulnerabilities. Emerging adulthood is characterized with instability, constant and quick changes as well as heterogeneity in the pace and order of transitional milestones among young people. It is a period that involves five major role transitions: leaving home, completing school, entering the workforce, forming a romantic partnership, and transitioning to parenthood [15,46]. It is a period when youth initiate adult roles and responsibilities [53–55] and establish patterns of positive and risky health behaviors that carry through to adulthood [56–58]. Specific to SSA, a region heavily impacted by HIV and poverty, emerging adulthood is particularly important because it is when individuals become increasingly sexually active, and thus are at an elevated risk of contracting HIV [43]. YPoAIDS are particularly vulnerable during this life stage because they are often subject to multiple relocations, and stigma and discrimination related to HIV/AIDS orphanhood [29,31,42,48,49]. This study offers a time-sensitive and unique opportunity to examine how small direct investments through an asset-oriented EEI package received during adolescence may have long-term effects as youth transition into emerging adulthood.

#### Asset theory

Asset theory posits that assets can lead to wide scale benefits, including expectations for more resources in the future, feelings of safety and security [59], and future planning [60,61]. Asset-building is increasingly viewed as a critical factor for reducing poverty, positively impacting attitudes and behaviors, and improving psychosocial functioning and stability [62–65]. Asset theory is consistent with several behavioral and psychosocial theories that have guided research on sexual risk-taking and health and mental health functioning, including the Bandura Social Cognitive Theory [66] and the Theory of Reasoned Action [67,68]. Asset-theory contributes to our understanding of how attitudes and beliefs evolve, thus influencing intentions and behaviors [59].

#### Overview of the *Original Bridges* study (2012–2018)

The overall goal of *the Original Bridges* study was to evaluate the efficacy and cost-effectiveness of the *Bridges* intervention (detailed below) for YPoAIDS. The study recruited 1383 school-going adolescents (average age 12.7 years). Participants were included if they met the following inclusion criteria: 1) an AIDS-orphaned child/adolescent, defined as one who had lost one or both parents to HIV/AIDS; 2) enrolled in school; 3) in the last two years of primary school; 4) between ages 10 to 16 years; and 5) living within a family (broadly defined and not an institution; institutions have different familial needs). Participants were ineligible if they were not able to comprehend the study procedures as assessed during the informed consent process. Participants were recruited from 48 primary schools in the greater Masaka Region of Uganda (Masaka, Rakai, Kyotera, Lwengo and Kalungu, five districts hardest hit by HIV/AIDS—prevalence 11.7% vs. 5.4% national average) [69]. Using a cluster-randomized controlled trial (RCT), 48 primary schools were randomly assigned to three study arms (n = 16 schools in each arm): 1) control arm receiving usual care, 2) the *Bridges* arm receiving a Child Development Account (CDA—see description in Fig 1) with a 1:1 match, financial education, and mentorship), and the *Bridges PLUS* arm receiving a CDA with a 2:1 match, financial education, and mentorship. The only difference between the two treatment arms was the match rate: 1:1 vs. 1:2. The match rate was specifically varied to address the incentivizing and cost-effectiveness question. As indicated in Fig 1 below, both *Bridges* and *Bridges PLUS* included the following intervention components that had been tested in two earlier studies [31–37].

**Fig 1 pone.0284572.g001:**
[figure not shown]
Description of bridges economic intervention components.

#### Progress of the *Original Bridges* study

*Economic stability*. The study filled important knowledge gaps on the effect of savings- led EEI on short-term economic stability. We found that several measures of material well‐being improved among participants in the treatment condition [74]. Specifically, *Bridges PLUS* arm participants had significantly lower odds of having only a few sets of clothes at both the 12‐month (OR = 0.49, 95% CI = 0.24, 0.97) and 24‐month follow‐ ups (OR = 0.36; 95% CI = 0.15, 0.85) compared to participants in the control group. In addition, *Bridges* arm participants had significantly lower odds of having no blanket at both the 12‐month (OR = 0.33; 95% CI = 0.12, 0.89) and 24‐ month follow‐ups (OR = 0.19; 95% CI = 0.06, 0.64) compared to participants in the control group [71]. In addition, the intervention increased the odds of owning a family business and the levels of asset holding. Families in both *Bridges* and *Bridges PLUS* arms had significantly higher odds of owning a small business at the 24‐month follow‐up (for *Bridges*: OR = 2.28; 95% CI = 1.05, 4.95; for *Bridges PLUS*: OR = 2.95; 95% CI = 1.38, 6.29) than families in the control arm. Both treatment arms reported a higher increase in their levels of asset possession from baseline to 12 months than the average increase in the control arm [10,74].

*Mental health functioning*. At 24-months post intervention initiation we found a significant unmediated effect of the intervention on children’s mental health (B = −0.59; 95% CI = 0.93, −0.25; p < 0.001; β = −0.33). Moreover, the results suggest that participation in the intervention reduced child poverty at the 12-month follow-up, which in turn improved latent mental health outcome at 24 months (B = −0.14; 95% CI: −0.29, −0.01; p < 0.06; β = −0.08). In addition, at 36 and 48-months, mental health of children in the treatment arms improved by 0.13 and 0.16 standard deviation points correspondingly with no evidence of mediation [75].

*Sexual Health*, *HIV Knowledge/Attitudes and Sexual Risk-Taking*. We found that in the short-run, adolescents in the intervention arms were more likely than control arm participants to report increased scores on HIV knowledge (*b* = .86, 95% *CI* = .47–1.3, *p* ≤ .001), better scores on desired HIV-related beliefs (*b* = .29, 95% *CI* = .06, .52, *p* ≤ .01), and better scores on HIV prevention attitudes (*b* = .76, 95%*CI* = .16, 1.4, *p* ≤ .01) [76–78]. We however acknowledge the potential self-report bias inherent in sensitive lines of inquiry that may have biased these reported short-term results.

*Educational Achievement*. At 24-months post-intervention, we found a 27-percentage point difference, with participants in the intervention arms exhibiting higher likelihoods of schooling at least 90% of the time over a 2-year period. Regarding other educational outcomes, on average, adolescents receiving both interventions showed lower dropout rates, a higher likelihood to take the Primary Leaving Examinations (PLE) and score higher on these PLEs [12,78].

*Cost-effectiveness*. The *Original Bridges* was the first study, to our knowledge, to examine the cost- effectiveness of a savings-led economic intervention based on matched savings accounts in SSA. We found that at 24-months post intervention, adolescents in both intervention groups showed better health, mental health, self-concept, self- efficacy, and HIV knowledge compared to those in the control condition [78]. Our analyses at 48-months indicated that intervention effects were sustained, and higher incentive matching positively impacted more outcomes than lower matching. Specifically, at 48-months, we found that *Bridges PLUS* significantly improved self-rated health (0.25, 95% CI 0.06–0.43), HIV knowledge (0.21, 95% CI 0.01–0.41), self-concept (0.26, 95% CI 0.09–0.44), and adherence self-efficacy (0.26, 95% CI 0.09–0.43), and lowered hopelessness (-0.28, 95% CI -0.43–0.125); whereas *Bridges* significantly improved only self-rated health (0.26, 95% CI 0.08–0.43) and HIV knowledge (0.22, 95% CI 0.05–0.39). Incremental Cost-Effectiveness Ratios (ICERs) ranged from $224 for hopelessness to $298 for HIV knowledge [10,11,78].

Overall, the *Original Bridges* data have made significant contributions to the literature on the short-term effects of savings-led EI interventions for YPoAIDS. However, we do not know for how long the observed short-term behaviors will be sustained, especially as participants transition through adolescence into young adulthood.

## Methods

### The current study

The *Bridges-R2* study will examine the longitudinal developmental and health outcomes [(e.g., sexual risk-taking behaviors, HIV antiretroviral therapy adherence, PrEP use (for those who are HIV negative)], optimizing health outcomes along the HIV care continuum, and potential mechanisms of the effect of protective health behaviors) of the *Bridges* cohort. Specifically, based on emerging adulthood [13,14] and asset theory [59,60], we expect that the Bridges program would impact youth developmental and health outcomes by reducing the vulnerabilities associated with orphanhood which interfere with the normal development, including reducing stigma and discrimination, improving family support, social support, hopefulness, general self-efficacy, and improve sexual communication skills, and overall facilitate healthier transitions into adulthood (see Fig 2A and 2B). The data will be collected at baseline following reconsenting, 12, and 24-months.

**Fig 2 pone.0284572.g002:**
[figure not shown]
A. Usual care for YPoAIDS. B. The bridges program.

### Inclusion criteria

All *Original Bridges* participants (N = 1383), regardless of number of completed follow-up interviews, will be eligible for *Bridges-R2*. The youngest participant will be 18+ years of age.

We will rely on the *Original Bridges* participants completed future contact forms, the community trust, including with the schools, and Masaka Diocese parish priests for re-consenting. The future contact forms completed by all enrolled participants, provide details on their last known home address, and a list of people who may know their whereabouts, even when they move. Through our field office located in Masaka, we recently confirmed our ability to track and reconsent the majority (>80%) of the 1249 participants from Wave 5 (N = 999).

### Sample tracking, retention and attrition

The *Original Bridges* study (2012–2018) had an attrition rate of 9.7%, leaving a total of 1249 participants at the end of the study (see Table 1). The reported low attrition rates, and the team’s ability to easily track and reengage participants over longer periods of time are attributable to: a) the study team having built trust with community members over the 17+ years; b) we have a fully-fledged field office in the Masaka region allowing for easy engagement between the study team and the local collaborators; c) the team has a well-established tracking system, with at least six NIH-funded studies resulting in very low attrition rates; d) unlike open cohort studies, the *Bridges* study participants have been engaged with the study team for an EEI as opposed to an open surveillance cohort. In such cases, the attrition rate tends to be low because of the active engagement and investment in the participants from the very start of the study.

**Table 1 pone.0284572.t001:** Bridges retention rates.

Baseline	Wave 2	Wave 3	Wave 4	Wave 5
N = 1383	N = 1321	N = 1221	N = 1228	N = 1249
Retention	95.5%	88.3%	88.8%	90.3%

In addition, the *Bridges* study took place in a highly stable region of Uganda where geographical moves among school-going adolescents are rare. The *Bridges-R2* will be conducted in the same region. During the re-consenting process, we will ask participants to update their future contact details, currently on file, with updated telephone number(s) (if they have one: 95% of participants report having access to a phone in the household), and an updated list of names and contact information of three people who will always know how to reach them. Participants will be reminded that if we contact the people listed, we will not discuss any details about their study participation. Like we have done in the past, we will use these records solely to help track their location and only if we have lost contact. We have effectively used these procedures in our previous research studies, as well as our most recent competitive renewal study with YLHIV [79]. Thus, we conservatively expect to re-consent at least 80% of the original sample; and we expect attrition from the reconsented participants to be no more than 20% by the end of the follow-up period. Power analyses (described in the statistical power analysis section) indicate our study is powered to detect medium standardized effects with attrition levels up to 20%, so the impact of attrition on power to test our proposed primary hypotheses for specific aims 1 and 2 should be minimal.

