### Statistical power analysis

Minimum detectable effect sizes were estimated using NCSS PASS [80] for the primary analyses proposed to fulfill primary specific aims 1 and 2. Assuming a 20% attrition rate between the end of the *Original Bridges study* (July 2017; N = 1249) and the *Bridges-R2* study (July 2022), our starting N for *Bridges-R2* will be 999 participants. Following a maximum attrition rate of 20%, we anticipate a minimum of 799 participants available at the final measurement wave. We further assume alpha = .017 and power = .80. For specific aim 1, we assumed a control group HIV prevalence of 19.7% based on published data for 15–24-year-old youth from the same geographic region [81] and an intraclass correlation (ICC) of .12 based on our current *Bridges* study data. Assuming these inputs, a two-level multilevel model would be able to detect a raw proportion difference of 15.3%, which corresponds to a standardized difference *h* = .499, which is a medium minimum detectable effect size [82]. For specific aim 2, we computed the minimum standardized mean difference *d* for a continuous mechanism of change outcome in a three-level multilevel model assuming the same inputs as above and a maximum within-participant ICC of .70 for the continuous change mechanisms in the *Bridges* study. Under these conditions, *d* = .462, which is a medium minimum detectable standardized mean difference [82].

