#### Time points used in proposed inferential analyses

To maximize the rigor of the analyses; to assure alignment of biomarker data (only measured in the *Bridges-R2*) and our remaining outcomes; and to avoid reuse of *Original Bridges* study outcomes (already examined for shorter-term intervention efficacy) and biased examination of longer-term intervention efficacy, all proposed primary inferential analyses and most of the proposed secondary inferential analyses listed will use only *Bridges-R2* data. The exception is longitudinal developmental trajectory analyses proposed to explore associations between changes in time-varying covariates and mechanisms of change with outcomes measured across both studies.

#### Primary analyses for Aim 1

We hypothesize that: H1a. Relative to the control group, participants in the *Bridges* intervention group (1:1 savings incentive match rate) will have a lower odds of HIV infection at the final measurement point; H1b. Relative to the control group, participants in the *Bridges PLUS* intervention group (1:2 savings incentive match rate) will have a lower odds of HIV infection at the final measurement point; and H1c. Relative to the *Bridges* intervention group, participants in the *Bridges* PLUS intervention group will have a lower odds of HIV infection at the final measurement point. To test H1a-H1c, we will fit a two-level generalized linear mixed model (GLMM) with fixed effects for study arm, time, and their interaction. We will use random intercepts for school ID to account for clustering of persons within schools. Reflecting the binary HIV status outcome, a binomial distribution and logit link will be used. To test H1a-H1c we will perform three pairwise planned comparisons. Alpha (α) will be set at .05/3 = .017 for these three comparisons to maintain a nominal α = .05. We will adjust for orphanhood status, the only covariate where imbalance was detected in our *Original Bridges* data. It is important to note that previously, deaths have been very few; however, if numbers of deaths become non- trivial, we will extend our proposed GLMMs to jointly model survival and the odds of HIV infection simultaneously [115].

#### Secondary exploratory analyses for Aim 1

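### The 80% re-consent target has two different bases (1383 and 1249), loss from randomisation (up to 42%) is never stated, and no correction is given for selection at re-consent

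*Protocol article*

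**What the plan says.** Under Inclusion criteria, the eligible group is everyone enrolled in Original Bridges: "participants (N = 1383), regardless of number of completed follow-up interviews, will be eligible for" R2. The same section reports a recent check of the field team's ability to "track and reconsent the majority (>80%) of the 1249 participants from Wave 5 (N = 999"), so there the 80% is taken of Wave 5.

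Under Sample tracking, retention and attrition, the first study "had an attrition rate of 9.7%, leaving a total of 1249 participants at the end of the study". The section then says "we conservatively expect to re-consent at least 80% of the original sample", followed by a loss of at most 20% among those re-consented. It concludes that power holds with attrition of as much as 20%, so that attrition should matter little for the primary hypotheses of Aims 1 and 2.

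Under Statistical power analysis, 20% is removed from 1249, so that "our starting N for *Bridges-R2* will be 999 participants". A further maximum loss of 20% gives a minimum of 799 at the last wave.

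Under Time points used in proposed inferential analyses, "all proposed primary inferential analyses and most of the proposed secondary inferential analyses listed will use only *Bridges-R2* data". The reasons given are alignment with biomarkers that exist only in R2, and avoiding re-use of outcomes already examined. The missing-data section plans maximum likelihood and multiple imputation under missing at random, with auxiliary variables and pattern-based sensitivity analyses. It does not say whether these extend to people who never re-consent.

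**The concern.** H1a-H1c compare randomised arms, so the natural denominator is the 1383 randomised. The article uses two bases for the same 80% and never combines its losses into one figure from randomisation. A reader of the attrition paragraph would take the comparison to be exposed to about 20% loss, when the planning numbers allow about twice that.

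The larger share of the loss falls before the first R2 visit. Someone who does not re-consent has no R2 record, and an analysis confined to R2 data has nothing of theirs to model. If re-consent depends on both arm and HIV risk, the arm contrast is biased, and a larger sample does not remove that.

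The article itself gives grounds for taking this seriously:
- The Introduction links rising HIV incidence to leaving school and migrating for work or marriage, events that also make people harder to trace.
- The intervention changed schooling (odds ratio 1.66 for moving to post-primary education; a 27-point difference in schooling at least 90% of the time), so a plausible driver of traceability differs by arm.
- Low attrition is credited partly to active investment in participants, but the control arm received usual care.
- The reassurance about few geographical moves concerns school-going adolescents, whereas every R2 participant will be 18 or older.

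**Working it through.** **Inputs.** Randomised and eligible: 1383 (Inclusion criteria). Wave 5: 1249 (Table 1). Re-consent: 80%. Loss within R2: at most 20%. Starting and final N: 999 and 799 (Statistical power analysis). Control prevalence 19.7%, intraclass correlation 0.12, alpha .017, power .80 (same section). Clusters: 48 schools, 16 per arm.

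**1. The sample chain.**
- 0.8 × 1249 = 999.2, stated as 999. Reproduced.
- 0.8 × 999 = 799.2, stated as 799. Reproduced.
- 0.8 × 1383 = 1106.4, which is not 999.

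So 999 comes only from the Wave 5 base; 999/1383 = 72.2%.

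**2. Loss from randomisation on the plan's minimum numbers.**
- Before the first R2 assessment: 1383 − 999 = 384, or 27.8%.
- Within R2: 999 − 799 = 200.
- Cumulative: 1383 − 799 = 584, or 42.2%; retained 799/1383 = 57.8%. Check: 0.903 × 0.80 × 0.80 = 0.578.

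On the attrition section's wording (80% of 1383), the chain would be 1106, then 885, a cumulative loss of 1 − 0.64 = 36.0%.

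**3. Does the base affect power?** Design effect = 1 + (799/48 − 1) × 0.12 = 2.877. Effective n per arm = (799/3)/2.877 = 92.6. A two-proportion test with pooled variance, two-sided alpha .017 (sidedness is not stated, so this is assumed) and power .80 gives a detectable difference of 15.33 points, h = .4985. The plan states 15.3 and .499, so its figure is reproduced at N = 799. At N = 885 the effective n is 95.4 and the detectable difference about 15.15 points. The base moves it by about 0.2 points.

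**4. How much could selection distort the contrast?** The documents give no retention by HIV status, so the ratios here are assumptions. Take 19.7% in every arm, no true effect, and retention unrelated to HIV status in the two intervention arms. In the control arm let r be the retention of HIV-positive relative to HIV-negative participants. Observed control prevalence = 0.197r/(0.197r + 0.803).
- r = 0.8: 0.1576/0.9606 = 16.4%, a false 3.3 points against the intervention.
- r = 1.25: 0.24625/1.04925 = 23.5%, a false 3.8 points in its favour.

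**The case against.** Much of the opposing case stands.

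- **Both percentages are ceilings.** The article gives 799 as a minimum and 80% as a lower bound on re-consent. Building on 999 also counts nobody from the 134 absent at Wave 5, although they are eligible. A reader might infer that 28% or more will fail to re-consent, or that 42% will be lost. The documents support only up to 28% and up to 42%.
- **The two stages differ.** A reader might infer that 42% of those randomised vanish from the primary comparison. They do not: the 200 or so lost after the first R2 assessment have an HIV assay from that visit, enter the model with arm, time and interaction, and are covered by the stated likelihood and imputation methods. The loss without stated handling is the part before that visit.
- **Each step is printed.** The 9.7%, the two 20% losses and the resulting Ns can all be found. The 20% sentence is about power, and the power figure already carries the full loss.
- **The R2-only rule concerns time points and outcomes.** The auxiliary variables are not limited by source, and the full protocol or analysis plan may say more. That tempers the point: the article does not exclude using earlier waves for people who never re-consent, but it states no such use, and its rule points the other way.
- **No differential re-consent has been shown.** The illustration can go in either direction.

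What the objection does not remove is the contradiction over the base of the 80%, or an attrition argument that cites one 20% step for a comparison of arms randomised three loss steps earlier.

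**Conclusion.** The point holds in a bounded form. The re-consent target is stated against two incompatible bases: 1106 by the attrition section, 999 by the eligibility check and the power section. On the plan's minimum numbers, up to 28% (384) of those randomised are lost before the first R2 assessment and up to 42% (584) by the final wave; neither figure appears in the article. The primary analyses are confined to R2 data and no correction for selection at re-consent is stated.

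The sample size is sound on this point, since 15.3 points reproduces at 799. Nor do the documents show that the estimated effect will be biased, or in which direction. The false differences of 3.3 and 3.8 points rest on assumed retention ratios of 0.8 and 1.25 in one arm only; they show that moderate differential selection could matter, not that it is expected.

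**What to change.** 1. State one re-consent target with its base. The figure consistent with the power section is at least 999, which is 72% of 1383 and 80% of Wave 5.
2. In the attrition section, replace the single 20% with the cumulative loss from randomisation, up to 42%.
3. Report re-consent and 24-month HIV testing by arm, with all 1383 as denominator.
4. Keep R2 outcomes as the only outcomes, and add a prespecified analysis of H1a-H1c that weights by the inverse probability of re-consent and of 24-month testing, or multiply imputes. Use Original Bridges baseline and whatever earlier-wave covariates are available, by arm. Earlier waves then serve only as predictors, which respects the plan's reason for not re-using earlier outcomes.

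This is proposed alongside the primary analysis. Making all 1383 the primary analysis set is debatable, because HIV was never assayed before R2.

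Cost: more analysis work and somewhat wider intervals (not computed here), with no new data collection. Earlier waves are themselves incomplete (Table 1 shows 1221 to 1321 of 1383 at follow-up waves), and the missing-at-random assumption for people never seen in R2 cannot be tested.
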